## Abstract

**Background:**

Debilitating Symptom Complexes Attributed to Ticks (DSCATT) is a new term for an unexplained Australian syndrome—people who suffer from a chronic, multifaceted and debilitating illness, characteristically attributed to tick bites, but in a country without endemic Lyme disease. Despite the profound morbidity of DSCATT, no single causative agent has been identified and there are no recognised treatments for the illness at present. An increasing body of evidence shows psychological therapies such as Acceptance and Commitment Therapy (ACT) can be effective in reducing symptom-related disability and improving quality of life for other unexplained syndromes. Here we present a study protocol to assess the feasibility of an ACT-informed intervention for patients suffering from DSCATT, to be used adjunctively to their pre-existing healthcare. The study aims to assess the acceptability, practicality and demand for the treatment. Additionally, we will examine the effects of therapy on participants’ health and well-being, its safety, potential mediators of response to therapy and its preliminary cost-effectiveness.

**Methods:**

We will assess the feasibility of a 32-week, randomised, waitlist-controlled, parallel convergent mixed-methods pilot trial for DSCATT. Participants will be randomised in a 1:1 ratio to receive either 16 sessions of ACT-informed therapy adjunctive to their pre-existing healthcare, delivered one-to-one with a trial therapist within a 20-week period or be assigned to the waitlist control group where they will continue their treatments as usual. We will collect quantitative and qualitative data to address study aims, with retention rate being the primary feasibility outcome.

**Ethics and dissemination:**

The study has ethical approval from Austin Health Human Research Ethics Committee (HREC). The outcomes will be published in peer-reviewed journals. Data from participants who have given extended consent will be available for other HREC-approved studies.

**Trial registration number:**

ACTRN12623000372684, prospectively registered 13 April 2023, URL: https://www.anzctr.org.au/Trial/Registration/TrialReview.aspx?id=385579&isReview=true; the last participant is expected to complete in November 2026.

STRENGTHS AND LIMITATIONS OF THIS STUDYFirst proposed clinical trial for Debilitating Symptom Complexes Attributed to Ticks (DSCATT).Mixed methods design to comprehensively explore the feasibility of a proposed intervention for DSCATT.Patient-centred psychology intervention to be used alongside pre-existing healthcare (excluding other psychological therapies).No agreed case definition for DSCATT exists; inclusion criteria for this trial established by modified Delphi process.No agreed outcome measure for DSCATT exists; exploratory DSCATT symptom scale developed for this trial.

## Introduction

 Ticks are parasites that feed on animal and human blood and can cause a range of illnesses to their hosts. Lyme disease is perhaps the most famous tick-borne disease, caused by infection with the bacteria *Borrelia burgdorferi* sensu lato complex, and is endemic in large parts of the northern hemisphere. In Australia, ticks can cause Rickettsial infections, allergic reactions and Mammalian Meat Allergy,^1^ but while many people have developed a ‘Lyme-like’ illness, none has been definitively attributed to Lyme disease acquired in Australia.^2^,^4^ No other infective cause has been identified for these cases following national accredited testing procedures,^4 5^ and while research surveying Australian tick populations has revealed novel bacterial and viral profiles,^6 7^ their impacts on human health are yet to be elucidated.

The presence, or absence, of Lyme disease in Australia has been a highly contentious and polarising issue. After a senate inquiry into Australian Lyme-like illness in 2016,^8^ the Australian Government recognised that there are a cohort of patients suffering from the symptoms of a chronic debilitating illness which many associate with tick bites. They described this patient group as having Debilitating Symptom Complexes Attributed to Ticks (DSCATT), in an attempt to acknowledge this patient group’s multifaceted illness and mitigate the stigma and controversy associated with Lyme terminology, such as Chronic Lyme Disease.

The prevalence and burden of DSCATT is unknown, though the Senate enquiry suggests a large number of people are profoundly affected.^9^ In addition, the pathophysiology of the illness is unclear, and diagnostic biomarkers and symptom criteria are yet to be established. After extensive medical investigations, individuals with DSCATT are usually left without a clear explanation for their illness and often feel that their symptoms and level of impairment are not believed by healthcare providers.^10^ We examined the records of 29 people with DSCATT and found no alternative medical explanation for their extensive and disabling symptoms in the great majority of cases,^11^ so that DSCATT may at present be considered a medically unexplained syndrome (MUS). Many had been diagnosed with various other MUS on their journey, so that its relationship with these is also uncertain.

There are no recognised treatments for DSCATT; however, there has been much research into treatments for other MUS.^12^,^14^ Even without established pathophysiological mechanisms, symptomatic and supportive care may improve symptom-related disability and quality of life. An increasing body of evidence shows that psychological therapies such as Acceptance and Commitment Therapy (ACT) can be effective in this way in MUS,^15^,^18^ as well as in other chronic health conditions such as cancer, chronic pain and stroke.^19 20^ ACT is a ‘transdiagnostic’ intervention which can be applied to individuals struggling with unwanted internal experiences (eg, physical sensations, unpleasant thoughts/feelings), regardless of their health condition or diagnosis.^21^ At its core, ACT aims to improve ‘psychological flexibility’ in the individual and equip them with the practical skills to take effective action to live according to their values, even in the face of pain and suffering.^22^ ACT may be particularly suited for patients with DSCATT by, for example, assisting them to identify meaningful personal values and develop goals matched to those values. Working with people who identified as having DSCATT, we developed a DSCATT-specific treatment informed by ACT, though including other therapeutic elements, and piloted the therapy in seven people who identified as having DSCATT (ACTRN12621001032842; manuscript in submission). Feedback was largely positive and those who completed the programme said they would recommend it to others.^23^

In this study, we propose a feasibility trial, given there are no published clinical trials or treatment reports for DSCATT, and given the controversy that can accompany psychotherapeutic interventions for MUS. As such, there is uncertainty around (a) the demand for, and acceptability of this type of treatment approach for DSCATT; (b) whether therapists will be able to deliver the therapy as per a standardised manual and (c) whether DSCATT patients will engage with the therapy itself. Further, there is uncertainty as to the value of the intervention to participants, and the measures that should be used to assess treatment efficacy. Therefore, we first need to assess if our therapy is practical, acceptable and in-demand for patients with DSCATT before a larger scale, treatment efficacy trial is conducted. Completion of this feasibility trial may also assist in identifying: (a) an appropriate primary outcome measure for future trials; (b) identifying factors which influence response to treatment (including expectations of treatment, and cognitions and behaviours related to illness); (c) changes in brain activity following treatment and (d) the preliminary cost-effectiveness data of the intervention.

We will use quantitative and qualitative data collection methods following a mixed-methods, parallel convergent design to provide a comprehensive and detailed understanding of the feasibility of the therapy for DSCATT. Further, this approach will provide insight into the effects of the therapy on patients’ health and well-being in the context of their DSCATT illness, and its safety profile.

## Study objectives

### Primary aim

Assess the feasibility of a 16-session ACT-informed treatment programme for adult patients with DSCATT. Markers of feasibility include practicality (including eligibility rate and treatment fidelity), acceptability (retention rate and satisfaction with treatment) and demand (including inquiry and participation rates). See table 1 for all feasibility markers used in the trial.

**Table 1 T1:** Feasibility outcomes

Area of focus	Feasibility research question/aims	Outcome measure and data source (quantitative or qualitative)	
		Quantitative	Qualitative
Acceptability	To what extent is the therapy judged as suitable, satisfying or attractive to participants with Debilitating Symptom Complexes Attributed to Ticks (DSCATT)?	Number of participants who do not withdraw prematurely from the programme (retention rate*) Treatment satisfaction questionnaire (satisfaction rate)	Reasons for premature withdrawal (field notes kept by project coordinator and/or trial therapist; semi-structured participant feedback interview) Satisfaction with treatment explored in semi-structured, post-treatment feedback interview
	What is the ability of participants to engage with the programme?	Number of sessions attended by participants (attendance rates)	Explored in semi-structured, post-treatment feedback interview
Demand	To what extent is the therapy likely to be used by patients with DSCATT (ie, how much demand is likely to exist?)	Number of people who express interest in the study (inquiry rate) Number of people who consent to participate in the therapy (participation rate)	Reasons for declining to proceed with the trial, obtained where possible (field notes kept by project coordinator)
Practicality	Is our screening process suitable to identify eligible candidates for randomisation into the trial?	Number of participants who are screened and deemed eligible for the trial (eligibility rate)	–
	Can the intervention be delivered as per a standardised therapist manual?	Therapist adherence to the intervention (treatment fidelity)	–
	Is it feasible to collect health service use via participant self-report and Medicare Benefits Scheme/Pharmaceutical Benefits Scheme (MBS/PBS) data access?	Completion rates of the self-report resource use questionnaire (RUQ) Number of participants who consent to MBS/PBS data access	–

* Primary outcome; measures adapted from Refs.^39^,^41^

### Secondary aims

Examine the effects of the therapy on participants’ health and well-being, and its safety profile (see table 2).

**Table 2 T2:** Clinical, safety and exploratory outcomes

Area	Measure	Timepoint
Clinical		
Quality of life	Assessment of Quality of Life 8-dimension scale (AQoL-8D)^42 43^	Baseline, Week 10, 20 and 32
Functioning	Work and Social Adjustment Scale (WSAS)^44^	Baseline, Week 10, 20 and 32
Depression, anxiety and stress symptoms	Depression, Anxiety and Stress Scale 21 (DASS-21)^45^	Baseline, Week 10, 20 and 32
Severity of illness and perceived improvement	Patient Global Impression scale (PGI)—severity and improvement^46 47^	Baseline (severity subscale only), Week 10, 20 and 32
Physical symptoms	30-item participant self-report Debilitating Symptom Complexes Attributed to Ticks (DSCATT) symptom scale developed by our research group	Baseline, Week 10, 20 and 32
Psychological flexibility	Comprehensive assessment of Acceptance and Commitment Therapy processes (CompACT)^48^	Baseline, Week 20 and 32
Clinician* rated severity of illness and perceived improvement	Transdiagnostic Clinical Global Impression (T-CGI) scale^49^	Baseline (severity subscale only), and treatment endpoint, that is, after completion of the participants 16th treatment session
Safety		
Safety of the intervention	Adverse events, as reported by the participant, and/or as observed by study staff	Assessed at each session by trial therapists; assessed at Week 10 and Week 20 by project coordinator (waitlist controls)
	Negative Effects Questionnaire (NEQ)—20 item^28^	Postintervention (Week 20) for therapy randomised, and treated waitlist controls
Exploratory		
Preliminary cost-effectiveness of the intervention	Healthcare resource use and cost, and lost productivity (absenteeism and presenteeism). Obtained via participant self-report on a tailored resource use questionnaire (RUQ) and supplemented by Medicare Benefits Scheme/Pharmaceutical Benefits Scheme (MBS/PBS) data from Services Australia (where specific consent is provided to access this data).	Baseline, Week 20 and Week 32 (RUQ); MBS/PBS data obtained for 3 months prior to randomisation (to reflect the same reporting time frame as RUQ) up until 8 months post randomisation
Brain activity	Task-based (emotional Stroop) and resting-state fMRI Blood Oxygen Level Dependent (BOLD) signal	Baseline and post-treatment (20 weeks after completion of the intervention)
Mediators of treatment response	Treatment expectancy measured by the Credibility Expectancy Questionnaire (CEQ)^50^	Baseline
	Cognitions and behaviours, as measured by the Cognitive Behavioural Response Questionnaire (short version; CBRQ-S),^51^ and the CompACT	Baseline and Week 20
Changes in clinical status of treated waitlist control participants	AQoL-8D, DASS-21, WSAS, physical symptoms, PGI data	Week 32 of RCT phase (treated waitlist controls’ baseline), and 10 weeks and 20 weeks after commencing the therapy

All measures are participant self-report, unless otherwise specified; baseline=prior to randomisation.

* Rated by the participant’s trial therapist.

RCT, Randomized controlled trial.

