## Methods and analysis

### Trial design

A 32-week, individually randomised, waitlist-controlled, parallel convergent mixed-methods feasibility and pilot trial involving adults (≥18 years) located in Australia with DSCATT. This study will collect quantitative and qualitative data to address its study aims.

Participants will be randomly assigned in a 1:1 ratio to receive 16 sessions of ACT-informed therapy, delivered one-to-one by a trial therapist within a 20-week period and adjunctive to their pre-existing healthcare with follow-up at 32 weeks OR participants will be assigned to the waitlist control group where they will continue their treatment as usual for 32 weeks. After control participants complete the 32-week waitlist, they will be offered access to the 16-session therapy with a trial clinician.

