**Figure 1 F1:**
[figure not shown]
Study procedures following informed consent. ^∧^Project coordinator contacts participant at Week 10 and Week 20 to review for AEs; *AEs reviewed by trial therapist in each treatment session, T-CGI completed by trial therapist pretreatment and post-treatment programme; **treatment programme participants only. Note: self-report questionnaires (during the RCT phase) will be administered at baseline (prior to randomisation), 10 weeks, 20 weeks and 32 weeks postrandomisation (irrespective of what session number the therapy randomised participants are up to in the treatment programme). ^#^Primary endpoint; ^~^follow up timepoint. Neuroimaging at the Melbourne Brain Centre Imaging Unit, Parkville, optional for participants (treatment group and treated waitlist group) to complete prior to commencing the treatment programme and repeated 20 weeks later/after their 16th therapy session—not shown on figure. ACT, Acceptance and Commitment Therapy; AE, adverse event; AQoL-8D, Assessment of Quality of Life-8 dimension; CBRQ-S, Cognitive Behavioural Response Questionnaire (short version); CEQ, Credibility/Expectancy Questionnaire; CompACT, Comprehensive assessment of Acceptance and Commitment Therapy processes; DASS-21, Depression Anxiety Stress Scale, 21 item; DSCATT, Debilitating Symptoms Complexes Attributed to Ticks; MINI, Mini International Neuropsychiatric Interview; NEQ, Negative Effects Questionnaire; PGI-S/I, Patient Global Impression scale (severity and improvement); RUQ, resource use questionnaire; SRQs, self-report questionnaires; T-CGI, transdiagnostic Clinical Global Impression scale; tx WL, treated waitlist; WSAS, Work and Social Adjustment Scale.

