#### Implementation

After satisfaction of inclusion criteria and completion of baseline questionnaires, participants will be randomised at a 1:1 ratio to the treatment intervention or waitlist-control arm, adjunctive to their treatment as usual. Randomisation will be completed by the project coordinator using the REDCap randomisation module.

The project coordinator will inform the participant of their group allocation following randomisation and determine their availability to commence sessions if allocated to the therapy arm. The participant will be assigned to a therapist based on matching availability. Participants randomised into the waitlist control group will be reminded of the trial timeline and opportunity to access therapy after 32 weeks.

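### The only post-baseline T-CGI rating is tied to finishing session 16, so it describes programme completers only, and its stated pre-randomisation baseline cannot be taken by a therapist assigned after randomisation

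*Protocol article*

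**What the plan says.** Table 2 (Secondary aims) lists the T-CGI among the clinical outcomes, with timing "Baseline (severity subscale only), and treatment endpoint, that is, after completion of the participants 16th treatment session". The footnotes to that table identify the rater ("Rated by the participant’s trial therapist") and define the first timepoint for the whole table ("baseline=prior to randomisation").

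Other sections bear on who can give this rating and when:

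- **Implementation.** Randomisation comes first. Then "The project coordinator will inform the participant of their group allocation following randomisation", and after that, for those allocated to therapy, "The participant will be assigned to a therapist based on matching availability".
- **Figure 1 legend.** "T-CGI completed by trial therapist pretreatment and post-treatment programme".
- **Trial design.** "After control participants complete the 32-week waitlist, they will be offered access to the 16-session therapy with a trial clinician".
- **Waitlist control arm.** Until Week 32, the contacts described are questionnaires and two coordinator calls about adverse events.
- **Blinding.** Trial therapists are among the unblinded parties.
- **Therapy arm.** Participants have 20 weeks in which to fit 16 sessions.
- **Clinical outcomes (Statistical methods).** Reporting is mainly descriptive, but limited between-group testing, treatment effect estimates with 95% CIs and a pooled SD are allowed, with no exception for the T-CGI.

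**The concern.** The T-CGI is the only clinician-rated clinical outcome. Its single follow-up rating exists only if the participant completes the programme. Retention is the primary feasibility outcome because early departure is a real possibility here, so a measure conditional on reaching session 16 is conditional on something close to that outcome. If people who stop early do less well, the T-CGI will look better than it would in everyone who began therapy. The trial is also meant to help identify a primary outcome for a later efficacy trial (Introduction), and the quantitative results feed that choice.

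Two further matters compound this. The rater is the unblinded therapist who delivered the treatment, and there is apparently no concurrent control rating. The stated baseline also cannot be right for this rater. A rating made by an assigned therapist is made with allocation already known, which is not what a reader of Table 2 would assume.

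**Working it through.** **1. Is the follow-up rating limited to completers?** The other measurements are scheduled as follows.

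| Measure | Follow-up timing | Available if session 16 is not reached? |
|---|---|---|
| Self-report questionnaires (Study questionnaires; Figure 1 legend) | Weeks 10, 20 and 32 (CompACT at Weeks 20 and 32 only), whatever session has been reached | Yes |
| Second MRI scan (Neuroimaging) | After session 16, or at Week 20 | Yes |
| Feedback interview (Feedback interview) | After the final session; also open to those withdrawn early | Yes |
| T-CGI (Table 2) | After session 16 | No time given |

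Among the clinical outcomes in Table 2, only the T-CGI depends on finishing the programme.

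**2. Can the baseline precede randomisation?** The order in Implementation is baseline questionnaires, randomisation, notice of allocation, then therapist assignment. The T-CGI rater is the assigned therapist, so that person's first rating must follow randomisation. The Figure 1 legend fits this order; the Table 2 footnote does not.

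**3. Can controls be rated?** The rater is the participant's trial therapist, and controls meet a trial clinician only after Week 32. The T-CGI is also missing from the Table 2 row of measures for treated waitlist participants. No sentence says that controls are unrated, so this is an inference.

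**4. The plan's own figure.** The exact (Clopper-Pearson) 95% interval for 72/120 is 50.7% to 68.8%, which rounds to the 51% to 69% given under Sample size estimation. It is reproduced and not in dispute.

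**5. Illustrative count.** Inputs: 120 randomised 1:1, so 120/2 = 60 per arm. Assumption: a proportion p of the therapy arm reaches session 16. The article gives no such figure, so p is varied over the retention rates it mentions.

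| p | With endpoint T-CGI, 60 × p | Without, of 60 | Share of all 120 randomised |
|---|---|---|---|
| 0.51 | 31 | 29 | 31/120 = 26% |
| 0.60 | 36 | 24 | 36/120 = 30% |
| 0.69 | 41 | 19 | 41/120 = 34% |

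The last column counts no waitlist ratings in the randomised phase. The range is a set of trial values for p, not a confidence interval for the therapy arm.

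**6. Form of the selection effect.** Let C be the mean result in completers and S the mean in those who start but stop early. The mean in all starters is pC + (1 − p)S, so reporting C alone differs from it by (1 − p)(C − S). If everyone allocated to therapy starts and p = 0.60, the difference is 0.40 × (C − S). The document gives no information on C − S, so no size can be stated.

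**The case against.** The T-CGI is one of seven clinical measures. The other six are self-reported in both arms at fixed weeks, and they include the patient-rated global impression, its natural counterpart. Clinical reporting is mainly descriptive, and the trial is not designed to detect a treatment effect. The rater and the lack of blinding are disclosed. The baseline mismatch looks like a generic footnote: the scan is also labelled baseline in Table 2, while the Neuroimaging section places it before the first treatment session. A full protocol may say what happens when someone stops early. Most of this stands, and it limits the importance of the point. It does not remove it, because the article states the timepoint explicitly and no later analysis plan can recover ratings that were never taken.

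Several stronger readings are tempting but unsupported:

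- **That the T-CGI is taken only after session 16.** A baseline severity rating is also planned; only the follow-up is restricted.
- **That at least 24 of 60 therapy participants will lack an endpoint.** The 60% is a precision example for study completion across both arms. Someone may finish session 16 and be lost before Week 32, or stay in the study having attended fewer sessions. The true count could fall on either side of 24.
- **That results will be inflated by a known amount.** The document says nothing about improvement in early stoppers.
- **That a planned between-arm T-CGI comparison is invalid.** None is specifically planned; the general wording merely fails to exclude one.

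It is also fair to object that a rating at discontinuation mixes short and full courses of therapy and still omits anyone who never starts. That is a real limitation of the remedy, and it is why sessions attended should be reported alongside.

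**Conclusion.** The point holds in a limited form. As written, the T-CGI endpoint covers only participants who complete 16 sessions, is scored by their own unblinded therapist, and apparently has no concurrent control. It may therefore look more favourable than in all who started therapy, by an amount the document does not allow anyone to estimate. The illustration of about 36 of 60 with an endpoint rating (31 to 41 over the range tried) rests on the assumption that reaching session 16 is about as common as the retention rates mentioned.

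The baseline contradiction is firm: the Table 2 footnote cannot apply to a therapist assigned after randomisation, and it disagrees with the Figure 1 legend. The absence of control ratings is an inference from several sections, not a statement in the text. The primary outcome and the sample size are unaffected. This should be corrected, but it does not threaten the trial's main purpose.

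**What to change.** 1. Collect the T-CGI endpoint for every participant who started therapy: after session 16 or, if that is not reached, at discontinuation or Week 20. The Week 20 fallback matches the Neuroimaging section. Report the number of sessions attended, and show completers separately as well.
2. Reconcile the Table 2 baseline with the Figure 1 legend and Implementation by stating a pretreatment baseline for the T-CGI, as an exception to the table footnote.
3. Describe the T-CGI as an uncontrolled, unblinded, within-programme measure, and place it outside the between-group tests and estimates allowed under Clinical outcomes.

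The cost is one short therapist rating per early stopper and a few words in Table 2 and the analysis text. The downside is that endpoint ratings will follow differing numbers of sessions, which the separate display of completers makes visible.
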